# **DATA MANAGEMENT**

The investigator team will monitor data frequently for quality and completeness. Data from source documents will be transferred into a case report forms (CRFs). All CRFs will be kept under lock and key, maintained by the Principal Investigator. Only authorized personnel (investigator and CRU study team) will have access to the participant study documentation.

The AKUH. N Clinical Research Unit (CRU) will be responsible for risk based monitoring. The following source data verification will be assessed as follows for all participants:

1. Eligibility check,
2. Informed consent process
3. Serious adverse events monitoring

In addition, ten percent of all participant charts will be randomly selected and assessed for 100% of source data verification and compliance with International Conference on Harmonization Good Clinical Practice (ICH-GCP). The Internal audit of the participant charts will be done by the Clinical Research Unit Quality Assurance Personnel, who will not be part of the study team. If significant issues are identified during the above noted review, additional participant charts will be selected for review to ensure protocol adherence, at the discretion of the CRU staff.

# **CONFIDENTIALITY**

All study documentation containing personal information relating to study subjects like consent forms and other documents that might link subject ID with other subject personal details will be kept in a secure locked area with limited access at Aga Khan University Hospital. Such documentation will only be made available to authorized personnel. These study documents will be made available to the investigators, clinical personnel who require this information to treat the patient and the above-mentioned personnel for inspection or auditing reasons. All electronic data kept at the investigator’s site will be kept secure. Computer access will only be made available to authorized personnel.

# **SAMPLE SIZE**

This is a pilot Phase 1b/2, proof of principle, study to determine safety and feasibility of a single dose LDRT for the treatment of severe Covid 19 pneumonia patients who have nearly exhausted conventional available options. Sample size is based on having sufficient patients to reasonably provide descriptive data for feasibility, toxicity and indication of efficacy:

- Cohort 1 (pre-Vent): 5 patients will be treated. If acute treatment related SAE is observed in ≤ 1 of 5 patients at 24h following LDRT, then 5 additional patients will be treated.
- Cohort 2 (on-Vent): 5 patients will be treated. If acute treatment related SAE is observed in ≤ 1 of 5 patients at 24h following LDRT, then 5 additional patients will be treated.

# **STATISTICAL ANALYSIS**

Descriptive statistics will be used to determine proportion of patients experiencing toxicity, improvement/worsening of oxygenation status, weaning off oxygenation or ventilation, discharge or death on/before 14d and on/before 28d. All endpoints will be summarized descriptively, using mean, median, interquartile range, minimum/maximum, and standard deviation for continuous endpoints, and frequency and percentage for categorical endpoints. The data from the 2 cohorts will be analysed independently.

# **ETHICS**

# **Study Conduct**

The trial will be conducted in compliance with the principles and guidelines of the Declaration of Helsinki (Version 2013), and to principles of Good Clinical Practice, Institutional Ethics Review Committee and regulations in Kenya.

# **Ethics Approval**

This protocol and supporting documentation will be submitted to Aga Khan University, Nairobi Institutional Ethics Review Committee for review and approval and to the Poisons and Pharmacy board (PPB) for review and approval. Implementation of the study will not occur until approvals from both entities are received. In the event the study shows benefit, the study team will seek approval from the AKUHN IERC and DSMC, the study could be expanded with the approval of the IERC to patients from outlying hospital could potential be transferred for a one-time treatment at the AKUHN RT unit. In addition, AKUHN investigator will train and assist colleagues at other RT units in Kenya to adopt this protocol in consultation with the regulatory authorities.

A research license will be sought from the National Council of Science, Technology and Innovation (NACOSTI).

Ethical approval from the IERC will be sought in separate amendment or protocol for the future analysis - for research purposes - of special labs collected.

# **Protocol amendments**

All amendments and modifications will be submitted to Aga Khan University, Nairobi Ethics Review Committee and Pharmacy and Poisons board for review and approval. No changes in protocol conduct will be implemented until approval is obtained from the Aga Khan University, Nairobi Ethics Review Committee and Pharmacy and Poisons board, unless required to eliminate apparent immediate hazards to the study participants.

# **Protocol deviations**

- Major Protocol violations and protocol deviations shall be reported to AKU, N IERC within 48 hours of the PI becoming aware of them
- Minor Protocol deviations will be reported to AKU, N IERC through a cumulative log with the annual continuing review report
- Major Protocol violations and protocol deviations shall be reported to the PPB within 7 days of the PI becoming aware of them.
- Minor Protocol deviations will be reported to PPB through a cumulative log with the annual continuing review report
- All deviations will also be summarized in the continuing review reports that are submitted AKU, N IERC and PPB
- Any suspensions (to include continuing review lapses), clinical holds (voluntary or involuntary), or terminations of this research by an IRB, the institution, the Sponsor, or regulatory agencies will be promptly reported to AKU, N IERC and PPB

# **Serious adverse events reporting**

SAEs and SUSARs will be reported as soon as possible, but within 48 hours of the site becoming aware of the event to AKUN, IERC.

SAEs and SUSARs will be reported as soon as possible, but within seven days of the site becoming aware of the event to PPB.

Follow up reports will be submitted as soon as available.

# **Unanticipated events**

All non-serious unanticipated problems (events not involving risk to participants or others) will be reported in the continuing review report to AKUN, IERC and PPB.

All serious unanticipated problems involving risk to participants or others should promptly (within 48 hours) to AKUN, IERC and to PPB within 7 days.

# **Continuing Review Reports**

The PI will be responsible for submitting the required continuing review report and supporting documentation to the AKUN, IERC and PPB, allowing sufficient time for review and continuation determination prior to the established continuing review date. A closeout report will be submitted at the end of the approved study duration, or upon completion of the study activities, whichever comes first.

# **Inspections and Audits**

Knowledge of any pending compliance inspections/visits by government agency concerning clinical investigation or research, the issuance of Inspection Reports, warning letters or actions taken by any Regulatory Agencies including legal or medical actions and any instances of serious or continuing noncompliance with the regulations or requirements will be reported immediately to AKUN, IERC

# **Data Safety Monitoring Committee (DSMC)**

An independent Data Safety Monitoring Committee (DSMC) will be established and will provide oversight for the conduct of this study. The DSMC will function independently to specifically determine SAE and relationship to study treatment at 24h following the treatment of each of the first 5 patients in Cohort 1. The DSMC will review pertinent aspects of the study to assess subject safety, compliance with the protocol, data collection, and risk-benefit ratio. Following the monitoring review, the chair will provide approval for the study to continue or be halted.

Study staff will get approval by the DSMC for opening the second cohort if in the opinion of the DSMC ≤ 1 of the 5 patients in cohort 1 have experience a treatment related SAE within 24h of treatment.

Additionally, the DSMC will be alerted in the event of any SAE and will meet within 24 hours. The adjudication of the SAE causality will be performed jointly in consensus by the PI and DSMC.

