# **PROTOCOL SUMMARY**

# **SYNOPSIS**

| Study description: | Hypothesis: Low-dose radiation therapy (LDRT) improves clinical, radiographic, and immune outcomes in hospitalized patients with covid-19 pneumonia and severe acute respiratory syndrome.  This study investigates LDRT as a selectively localized anti-inflammatory treatment to induce focal suppression of pulmonary immuno-toxicity within viral pneumonia infiltrates in hospitalized patients with COVID19.  Study: Administration of low dose whole lung radiotherapy (LDRT) for the treatment of severe COVID 19 pneumonia in patients on or requiring mechanical ventilation |
| --- | --- |
| Objectives: | To investigate safety and feasibility (primary endpoint) of low dose whole-lung radiation therapy (LDRT) in critically-ill patients with COVID-19 pneumonia, and to explore secondary efficacy endpoints: (1) clinical, (2) respiratory, and (3) outcome  **Primary Objective:**   1. To assess the feasibility and safety of administering LDRT to patients with severe Covid 19 pneumonia 2. To assess the toxicity of a single dose of LDRT administered to patients with severe Covid 19 pneumonia   **Secondary Objective:**   1. To assess improvement in oxygen requirement within 3 days following LDRT 2. To determine ability to come off mechanical (or avoid mechanical) ventilation within 7 days following LDRT 3. To determine time to discharge following LDRT 4. To determine time to death following LDRT |
| Endpoints | Primary   1. Safety/Feasibility – ability to complete LDRT without treatment related SAE 2. Toxicity – vital signs to assess clinical and respiratory status at 24h following LDRT   Secondary   1. Efficacy - ability to be weaned off pre-LDRT ventilatory or oxygen support at 3d post LDRT (% of patients) 2. Efficacy – ability to come off (or avoid) ventilatory support at 7d post LDRT (% of patients) 3. Efficacy - discharge or death by 14d / 28d post LDRT (% of patients) |
| SAMPLE SIZE | Up to 20 participants will be enrolled on this study.   - Cohort 1 (pre-Vent): Up to 10 participants - Cohort 2 (on-Vent): Up to 10 participants |
| Study population | 1. Patient with rtPCR and Xray/CT proven Covid 19 pneumonia who have not responded to conventional therapy and:   Cohort 1: would need mechanical ventilation if condition worsens (pre-Vent)  Cohort 2: has been on mechanical ventilation, but for not more than 5 days (on-Vent) |
| Phase: | Pilot Phase 1b/2 study |

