| Description of sites/facilities enrolling patients: | 1. AKUHN – a collaborative effort of the Clinical Research Unit, Dept. of Haematology-Oncology (radiation therapy section), infectious diseases, critical care |
| Description of study intervention: | 1. Single dose of 100 cGy LDRT administered to both lungs within 48h of determining eligibility 2. Cohort 1 : 5 patients will be treated. If acute treatment related SAE is observed in ≤1 of 5 patients, additional 5 patients will be treated. 3. Cohort 2 : 5 patients will be treated. If acute treatment related SAE is observed in ≤1 of 5 patients, additional 5 patients will be treated.   If > 1 of the initial 5 patients in either cohort experiences acute treatment related SAE, enrollment to that cohort will be halted. |
| Study Duration: | 3 months |
| Participant duration: | 28d from enrollment |

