# **Data Safety Monitoring Committee (DSMC)**

A Data Safety Monitoring Committee (DSMC) composed of 3 individuals (clinician, clinical investigator, statistician) not involved in the study will be constituted that will review the outcome of each of the first 5 patients in each cohort at 24h following treatment. If >1 of the initial 5 patients experience an SAE felt to be related to LDRT by the investigator and/or DSMC, the study will be halted. If ≤ 1 patients experience a related SAE, a total of 10 patients in each cohort will be enrolled. Any SAE observed in any of the additional patients will be reported to the DSMC for review and discussion.

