# **Justification for the separate cohorts**

It is unclear as to the optimal time to intervene with LDRT in the setting of cytokine storm and ARDS. Patients having been on ventilatory for a prolonged time period may have irreversible pulmonary damage and thus not respond to the anti-inflammatory effects of a single dose of LDRT and potential suffer toxicity. We thus plan to enrol 2 distinct cohorts of patients on this study so as to separate patients who may have irreversible lung damage (prolonged ventilation) from those who not yet been placed on a ventilator. Cohort 1 will be patients who have thus far been on various non invasive O2 supplementation (e.g. nasal canula, venti-marks, rebreather mask, non-rebreather mask), and their condition does not appear to be improving or may be worsening and are at risk of requiring intubation (pre-Vent). Cohort 2 will be those patients who are already on ventilatory support for a maximum of 5 days. Each cohort will enrol independently and assessed independently.

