# **RECRUITMENT AND INFORMED CONSENT**

The study will recruit patients hospitalized at AKUHN who meet eligibility criteria and can provide consent.

The study will recruit up to twenty **(20)** patients hospitalized at AKUHN who meet eligibility criteria and can provide consent. We intend to pre-screen approximately twenty-five (**25**) to **e**nrol the target number of patients.

The study will enrol 2 cohorts of patients, those that are on maximum oxygen support and are at risk of needing mechanical ventilation (Cohort 1: pre-Vent) and those who are already on mechanical ventilation (Cohort 2: on-Vent). Enrolment of each cohort will be done simultaneously and independently. Patients in Cohort 1 will likely be able to provide consent on their own. Patients on mechanical ventilation will need next of kin to provide consent. Procedures for both have been outlined and we have experience with the processes in the context of infection control guidelines for Covid19.

Eligible study participants (or next of kin) will be informed about the trial through an informed consent process conducted by the study investigators. Patients (or next of kin) will then be provided with the informed consent form and given time to review the information therein, ask questions and seek clarification before providing consent.

Institutional infection control policies for COVID-19 and similar highly transmissible and infectious viruses requires that no content should be taken out from a COVID-19 patient’s room except for the purpose of incineration and disinfection. For patients providing informed consent, the following process will be used to ensure the compliance with the ICF process:

- Consent information will be presented to patient by a study team member in the presence of a witness who is not a study team member.
- If patient agrees to participate in the study, he/she will sign and date the consent form.
- The investigator will take a photograph of the signed consent document.
- Photo image of the signed signature page of the consent form will be printed.
- The witness together with the person administering consent will sign and date the printed ICF.
- This will be placed in the subject’s chart.
- A printed copy of the fully signed ICF will be given to the participant or emailed to them.
- The Investigator will make a note in the patient’s medical record documenting the patient’s consent to participate in the study.

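### The protocol gives conflicting rules on when Cohort 2 may open and on what is halted after more than one related SAE in the first five patients

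*Protocol*

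**What the plan says.** The trial has a pre-vent cohort (Cohort 1) and an on-vent cohort (Cohort 2), each starting with five patients and able to grow to ten. The Synopsis sets the cap: "Up to 20 participants will be enrolled on this study". Section 15 states the continuation count separately for each cohort: "If acute treatment related SAE is observed in ≤ 1 of 5 patients at 24h following LDRT, then 5 additional patients will be treated". Section 6.1.1 gives the same count but is silent on the order of opening and on what a failed count stops.

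**Order of opening.** Section 11: "Enrolment of each cohort will be done simultaneously and independently". Section 6.1.5 agrees on independence but does not mention timing: "Each cohort will enrol independently and assessed independently". Section 17.9: "Study staff will get approval by the DSMC for opening the second cohort", on condition that the committee finds no more than one treatment-related SAE within 24 h among the five Cohort 1 patients.

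**Scope of a halt.** In the Synopsis, if more than one of the first five in either cohort "experiences acute treatment related SAE, enrollment to that cohort will be halted". Section 6.1.2 uses the same count, with relatedness judged "by the investigator and/or DSMC, the study will be halted". Section 17.9 also has the chair approve continuing or halting the study as a whole.

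**Routine 24 h review.** Section 6.1.2 has the committee review the first five patients of each cohort. Section 17.9 describes the 24 h determination only for "each of the first 5 patients in Cohort 1".

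**The concern.** The analysis is otherwise descriptive, and this is the protocol's one numerical rule for continuing. It decides which critically ill patients are irradiated, how many are treated before any safety check, and whether the on-vent cohort is studied at all. A cohort that opens only on another cohort's result is neither simultaneous with it nor independent of it. Staff who follow section 11 could treat a first ventilated patient whom section 17.9 does not yet allow. If a cohort fails its count, the site and the committee could each point to a section that supports a different action, and nobody could say afterwards which action followed the protocol.

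**Working it through.** **Plan's own figure.** Two cohorts of 5 + 5 patients: 2 × (5 + 5) = 20, which reproduces the cap in the Synopsis. No stated number is wrong. The fault lies in the logic of the rule.

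**One event pattern under each text.** Suppose 2 of the first 5 patients in Cohort 1 have a related SAE within 24 h.

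| Text followed | Consequence for Cohort 2 |
|---|---|
| Synopsis with section 11 (and 6.1.5) | Continues; only Cohort 1 enrolment is halted |
| Section 6.1.2 | Halted with the whole study |
| Section 17.9 | Not opened |

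**How often the readings diverge.** The protocol gives no related-SAE rate, so the per-patient rate p is an assumption, taken as equal and independent in the two cohorts and shown over a range.

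- One cohort triggers: h = P(at least 2 of 5) = 1 − (1 − p)^5 − 5p(1 − p)^4. At p = 20%: 1 − 0.3277 − 0.4096 = 0.2627.
- Under section 17.9, h is also the probability that Cohort 2 never opens. Under section 11 with cohort-level halting, Cohort 1's events have no bearing on Cohort 2.
- Study-wide halt if either cohort's count is enough (section 6.1.2, both first fives evaluated): 1 − (1 − h)^2. At p = 20%: 1 − 0.7373^2 = 0.456.
- Both cohorts stopped when each is halted only on its own count (Synopsis): h^2. At p = 20%: 0.2627^2 = 0.069.

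| Assumed p | One cohort triggers; Cohort 2 never opens under 17.9 | Study-wide halt, either cohort (6.1.2) | Both stopped on own counts (Synopsis) |
|---|---|---|---|
| 5% | 2.3% | 4.5% | 0.05% |
| 10% | 8.1% | 15.6% | 0.7% |
| 20% | 26.3% | 45.6% | 6.9% |
| 30% | 47.2% | 72.1% | 22.3% |

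**Exposure before Cohort 1 has cleared.** Under section 17.9 only Cohort 1's first five can have been treated: 5. Under section 11 with a separate count for each cohort, Cohort 2 can pass its own count and fill to ten while Cohort 1 is still within its first five: 5 + 10 = 15 at most.

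**The case against.** The best defence concerns the review limb. A reader might infer that Cohort 2's first five escape the committee altogether. The documents do not support that. Section 6.1.2 includes them. Sections 7 and 17.9 both have the committee alerted to SAEs and meeting within 24 hours, with causality settled jointly with the principal investigator, and neither limits this to Cohort 1. Since the count uses only related SAEs, any Cohort 2 event that could matter to it still reaches the committee. What differs between the sections is the routine 24 h look at Cohort 2, including patients without an SAE. The conflict there is between sections 6.1.2 and 17.9 alone, because the Synopsis and section 15 give per-cohort counts without mentioning the committee.

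Two other limits are fair. Only section 11 says the cohorts enrol at the same time; section 6.1.5 says only that they are independent. The larger probabilities also need high assumed rates. The protocol expects little acute toxicity and reports none in the ten patients of the earlier study it describes, so the lower rows of the range must be shown as well. Equal rates in the two cohorts are a simplification.

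It could also be argued that section 6.1.2 uses the word study loosely for a cohort. The Synopsis separates the cohorts expressly, and section 17.9 again speaks of the study continuing or being halted, so the text does not settle the matter. Nothing in the protocol reconciles the two opening rules.

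**Conclusion.** The point stands on order of opening and on scope of halting: each has two incompatible statements in the current text. The review mismatch is real but lesser. The contradiction needs no assumed rate. The probabilities only show how far the readings part: 2.3% to 47.2% for a single cohort, and 4.5% to 72.1% for a study-wide halt, over assumed rates of 5% to 30%, equal and independent in the cohorts. They are not forecasts. The exposure contrast of 5 against up to 15 patients follows from the enrolment rules alone.

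A reader might also infer that cohort-level halting must be the intended rule because section 16 analyses the cohorts separately. That section concerns data analysis, not stopping, and does not decide the question. The choice belongs to the sponsor and the committee.

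**What to change.** The sponsor and the committee should reconcile the Synopsis and sections 6.1.1, 6.1.2, 6.1.5, 11, 15 and 17.9 into one rule, stated once and cross-referenced elsewhere. It should fix three things:

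1. whether Cohort 2 opens alongside Cohort 1 or only after Cohort 1's first five have passed;
2. whether a failed count halts the affected cohort or the study;
3. which patients receive the committee's routine 24 h review.

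The cost is a wording amendment. Under section 17.3 it needs approval from the ethics review committee and the Pharmacy and Poisons Board before conduct changes, which takes time in a study planned for three months. If sequential opening is kept, Cohort 2 starts later. No extra patients or procedures are needed.

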# **STUDY RELATED INJURY**

Upon receipt of the IERC Approval, this study will be added to the AKU insurance/indemnity schedule of clinical trials, to cover the cost of injury resulting from their participation in this study.

# **COMPENSATION**

Participants will not be paid for taking part in this study. However, participants will each receive a self-care package (masks, gloves, and 50ml bottle of sanitizer) at the time of discharge from the hospital,

